# Impact of the duration of antibiotics on clinical events in patients with *Pseudomonas aeruginosa* ventilator-associated pneumonia: study protocol for a randomized controlled study

**DOI:** 10.1186/s13063-017-1780-3

**Published:** 2017-01-23

**Keywords:** Antibiotic, Antibiotic resistance, Bacterial infection, Bacterial pneumonia, Intensive care, Nosocomial infections, *Pseudomonas aeruginosa*, Respiratory tract infection, Ventilator-associated pneumonia

## Abstract

**Background:**

Ventilator-associated pneumonia (VAP) accounts for 25% of infections in intensive care units. Compared to a long duration (LD) of antibiotic therapy, a short duration (SD) has a comparable clinical efficacy with less antibiotic use and less multidrug-resistant (MDR) pathogen emergence, with the exception of documented VAP of non-fermenting Gram-negative bacilli (NF-GNB), including *Pseudomonas aeruginosa* (PA). These results have led the American Thoracic Society to recommend SD therapy for VAP, except for PA-VAP. Thus the beneficial effect of SD therapy in PA-VAP is still a matter of debate. We aimed to assess the non-inferiority of a short duration of antibiotics (8 days) versus prolonged antibiotic therapy (15 days) in PA-VAP.

**Methods/design:**

The impact of the duration of antibiotics on clinical events in patients with *Pseudomonas aeruginosa* ventilator-associated pneumonia (iDIAPASON) trial is a randomized, open-labeled non-inferiority controlled trial, conducted in 34 French intensive care units (ICUs), comparing two groups of patients with PA-VAP according to the duration (8 days or 15 days) of effective antibiotic therapy against PA. The primary outcome is a composite endpoint combining day 90 mortality and PA-VAP recurrence rate during hospitalization in the ICU. Furthermore, durations of mechanical ventilation and hospitalization, as well as number and types of extrapulmonary infections or acquisition of MDR pathogens during the hospitalization in the ICU will be recorded. Recurrence with predefined criteria (clinical suspicion of VAP associated with a positive quantitative culture of a respiratory sample) will be evaluated by two independent experts.

**Discussion:**

Demonstrating that an SD (8 days) versus LD (15 days) therapy strategy in PA-VAP treatment is safe and not associated with an increased mortality or recurrence rate could lead to a change in practices and guidelines in the management of antibiotic therapy of this frequent ICU complication. This strategy could lead to decreased antibiotic exposure during hospitalization in the ICU and in turn reduce the acquisition and the spread of MDR pathogens.

**Trial registration:**

ClinicalTrials.gov: NCT02634411. Registered on 19 November 2015.

**Electronic supplementary material:**

The online version of this article (doi:10.1186/s13063-017-1780-3) contains supplementary material, which is available to authorized users.

## Background

Ventilator-associated pneumonia (VAP) is a major cause of morbidity and mortality in intensive care units (ICUs), accounting for 25% of infections in these units [1]. From 1975 to 2003, the incidence of hospital-acquired pneumonia caused by *Pseudomonas aeruginosa* (PA) has almost doubled, increasing from 9.6% to 18.1% [2], and PA is the most frequently isolated Gram-negative aerobic bacterium from ICUs in a US national large-scale survey (23%) and the most frequent bacterium isolated from the respiratory tract (32%) [3]. PA-VAP is associated with a high mortality ranging from 40% up to 69% [4–7] and with rates of recurrence more than 30% despite adequate antimicrobial therapy [7–9].

More than 60% of all ICU patients receive antibiotics during their hospitalization [10]. It is critical to reduce antibiotic exposure of ICU patients without compromising patient safety, and in particular without more recurrences. Hence, few studies have reported the recurrence rate according to the antibiotic therapy duration. In a randomized non-inferiority trial comparing 8 days versus 15 days of antibiotic duration strategies for VAP, the mortality and recurrence rate 28 days after bronchoscopy did not significantly differ between groups [9]. However, patients with VAP caused by non-fermenting Gram-negative bacilli (NF-GNB), including PA, had a higher rate of recurrence with short-duration (SD) therapy compared to a long-duration (LD) therapy group [9]. These results have led the American Thoracic Society to recommend SD therapy for VAP, with the exception of VAP with NF-GNB, including *Pseudomonas aeruginosa* (PA-VAP) [11]. Nevertheless, many trials have shown that decreased antibiotic duration for PA-VAP would be safe and not associated with more recurrences or increased mortality [12, 13]. Hence, in a multicentric, randomized, controlled trial (the ProVAP study), an antibiotics discontinuation strategy according to serum procalcitonin concentrations allowed antibiotic exposure to be reduced without increasing recurrences or mortality, even though PA was the most frequently isolated bacterium [14]. Recently, duration of adequate antibiotic therapy was found to be not associated with treatment failure in a retrospective cohort of patients with PA-VAP [7]. Moreover, three trials [15–17] and a Cochrane meta-analysis [18] failed to demonstrate that a short fixed-course (7 or 8 days) antibiotic therapy could be associated with an increase in mortality or recurrence rate for patients with a pneumonia documented with PA or other NF-GNB. Finally, a recent meta-analysis concluded that the two strategies did not differ in terms of 28 day mortality, but because of lack of power, these conclusions remain a matter of debate [19].

Thus, whereas SD therapy strategy has shown its efficacy and safety in patients with VAP non-caused by NF-GNB, allowing decreasing antibiotic exposure without excess morbidity or mortality, its use in patients with documented VAP of NF-GNB remains a matter of debate. The impact of the duration of antibiotics on clinical events in patients with *Pseudomonas aeruginosa* ventilator-associated pneumonia (iDIAPASON) study was thus designed to evaluate this important clinical issue.

## Methods/design

The study is a randomized, open-labeled non-inferiority trial comparing two parallel groups: those receiving 8 days of antibiotic therapy (short duration, SD) and those receiving 15 days of antibiotic therapy (long duration, LD).

### Study population

Patients aged ≥18 years, diagnosed with ventilator-associated pneumonia documented with *Pseudomonas aeruginosa* (PA-VAP), affiliated to French social security, and providing a written informed consent signed by themselves or their next of kin are eligible for inclusion. The diagnosis of PA-VAP will include a clinical suspicion (≥ two criteria including fever > 38.5 °C, leukocytosis > 10^9^/L or leukopenia < 4.10^8^/L, purulent tracheobronchial secretions, and a new or persistent infiltrate on chest radiography) and confirmation by a *Pseudomonas aeruginosa* positive quantitative culture of a respiratory sample: bronchoalveolar lavage fluid (significant threshold ≥10^4^ colony-forming units (CFU)/mL) or plugged telescopic catheter (significant threshold ≥10^3^ CFU/mL) or quantitative endotracheal aspirate distal pulmonary secretion samples (significant threshold ≥10^6^ CFU/mL) [20].

Patients are not eligible in case of the following conditions: pregnancy, immunosuppression (HIV, immunosuppressive therapy, corticosteroids >0.5 mg/kg per day for more than a month), current antibiotic therapy active on PA for extrapulmonary infection, procedure of withdrawing life-sustaining treatment, chronic pulmonary colonization with *Pseudomonas aeruginosa* (chronic obstructive pulmonary disease (COPD) or bronchiectasis, with a positive respiratory sample below the threshold rate for *Pseudomonas aeruginosa* (i.e., <10^3^ CFU/mL for protected specimen brush or <10^6^ CFU/mL for tracheal aspirate), obtained in the absence of pneumonia or exacerbation during the 6 months before the ICU admission).

Antibiotic treatment should be started just after realization of bacteriological sampling, without waiting for the result. The choice of initial antibiotic therapy will be left to the discretion of the physician according to usual care based on the clinical context, previous antibiotic therapy, the presence or absence of risk factors for multidrug-resistant (MDR) pathogen antibiotics or hospitalization in the previous 90 days (current hospitalization ≥5 days, mechanical ventilation ≥5 days, support in a dialysis center or residency in a nursing home), local epidemiological data, and finally knowledge that the patient is already known as being colonized by a MDR pathogen. In these situations, a broad-spectrum antibiotic will be recommended immediately, with the association of a β-lactam/β-lactamase inhibitor or an antipseudomonal cephalosporin, and an aminoglycoside or an antipseudomonal fluoroquinolone for 3 to 5 days. An initial antibiotic with a narrow spectrum will be accepted in the face of early onset pneumonia (mechanical ventilation <5 days) and in the absence of risk factors for MDR pathogens and in accordance to the marketing authorization (AMM), contraindications, dosing recommendations, and drug interactions (http://base-donnees-publique.medicaments.gouv.fr/). Investigators are strongly encouraged to convert this initial regimen into a narrow-spectrum therapy, based on culture results. All antibiotics would be withdrawn, either at the end of day 8 or day 15, according to the randomization assignment, except those prescribed for a documented pulmonary infection recurrence or a new extrapulmonary infection before that day. The patient will be randomized just after antibiotic susceptibility test results and assigned to the SD arm or the LD arm. Screening of MDR pathogens will be realized with a surveillance culture of swab samples from the rectum for extended-spectrum β-lactam-producing Enterobacteriaceae (ESBL) and of swab samples from the anterior nares for methicillin-resistant *Staphylococcus aureus* (MRSA) at the patient’s admission in the ICU, and then once weekly until the patient’s discharge from the ICU (see Figs. 1 and 2).

**Fig. 1 Fig1:**
[figure not shown]
Conduct of the study. Study protocol flowchart. *SAPS* 2: Simplified acute physiology score II; *SOFA:* Sequential organ failure assessment; *CPIS:* clinical pulmonary infection score

**Fig. 2 Fig2:**
[figure not shown]
Template of recommended content for the schedule of enrollment, interventions, and assessment. *SAPS 2*: simplified acute physiology score (SAPS II); *SOFA*: sequential organ failure assessment (SOFA) score; *CPIS*: clinical pulmonary infection score

[name] (chair)	CHU La Pitié-Salpêtrière, Paris
[name]	CHU La Pitié-Salpêtrière, Paris
[name]	URC-Est, Paris
[name]	CH Chartres
[name]	CHU Beaujon, Paris
[name]	CHU Amiens
[name]	Hôpital Européen Georges Pompidou, Paris
[name]	CHU Clermont-Ferrand
[name]	Hôpital Nord, Marseille
[name]	CHU Bichat, Paris
[name]	CHU Bordeaux
[name]	Clinique Ambroise Paré, Neuilly-sur-Seine
[name]	CHU Rouen

The study will be performed in 39 French adult ICUs (Table 1). This work is supported by institutional grants from the French 2014 Programme Hospitalier de Recherche Clinique National (PHRC P140923 – AOM14515). The study is sponsored by the Clinical Research and Development Department of Assistance Publique – Hôpitaux de Paris. The sponsor had no role in the study design, collection, management, analysis, or interpretation of data, writing of the report, or the decision to submit the report for publication. The total duration of the study will be 27 months, including the inclusion period (24 months) and the duration of participation per patient (90 days).

### Objectives

The primary objective will be to assess the non-inferiority of a short duration of antibiotics (8 days) compared to prolonged antibiotic therapy (15 days) in *Pseudomonas aeruginosa* ventilator-associated pneumonia (PA-VAP) on morbidity-mortality at 90 days.

The secondary objectives will be to compare between short and long durations of antibiotics regarding:Mortality in the ICUMorbidity in the ICU (mechanical ventilation, duration of hospitalization)Exposure and acquisition of MDR pathogens during hospitalizationNumber and types of extrapulmonary infections

### Assessment criteria

The primary assessment criterion will be a composite endpoint combining day 90 mortality and PA-VAP recurrence rate during hospitalization in the ICU (within 90 days). Recurrence will be defined with a post hoc analysis by two independent experts with predefined criteria: clinical suspicion of VAP (≥ two criteria including: fever >38.5 °C, leukocytosis >10^9^/L or leukopenia <4.10^8^/L, purulent tracheobronchial secretions, and a new or persistent infiltrate on chest radiography) associated with a positive quantitative culture of a respiratory sample (bronchoalveolar lavage fluid (significant threshold ≥10^4^ CFU/mL), plugged telescopic catheter (significant threshold ≥10^3^ CFU/mL), or quantitative endotracheal aspirate distal pulmonary secretion samples (significant threshold ≥10^6^ CFU/mL)). In cases of disagreement between the two experts, a third expert will reach a consensus. Thereby, the percentage of patients with PA-VAP recurrence and/or death will be assessed.

Secondary assessment criteria will be 30 day and 90 day mortality rate, PA-VAP recurrence rate, mechanical ventilation (MV)-free days, ICU-free days, antibiotic-free days during the hospitalization in the ICU, number and types of extrapulmonary infections during the hospitalization in the ICU, and acquisition of MDR pathogens during the hospitalization in the ICU (from swab sample of rectum and anterior nares).

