### Statistical analysis

The study is designed to demonstrate the non-inferiority on the composite endpoint of mortality and recurrence at 90 days of the 8-day strategy versus the 15-day strategy for PA-VAP. Considering the mortality and/or recurrence of PA-VAP rate of 35.7% [7], 284 patients will be required in each group to achieve a power of 80% to exclude a 10% difference between the two groups with an α risk of 5%. To account for a possible 5% patient loss to follow-up, we planned to enroll 600 patients.

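### The white-cell limits printed in the eligibility and recurrence definitions appear ten times too low, so the clinical-suspicion test in effect needs one sign fewer

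*Protocol article*

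**What the plan says.** The protocol article states the white-cell sign twice. Under Study population, as part of the diagnosis needed for inclusion, it reads "leukocytosis > 10^9^/L or leukopenia < 4.10^8^/L". Under Assessment criteria, as part of recurrence in the primary endpoint, it reads "leukocytosis >10^9^/L or leukopenia <4.10^8^/L". The numbers are identical, and no other section gives a different value.

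In both places the white-cell sign is one of four listed. For inclusion the text is "The diagnosis of PA-VAP will include a clinical suspicion (≥ two criteria including fever > 38.5 °C" and for recurrence it is "clinical suspicion of VAP (≥ two criteria including: fever >38.5 °C". The list ends with "purulent tracheobronchial secretions, and a new or persistent infiltrate on chest radiography".

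Both definitions also require microbiology. For recurrence, the clinical suspicion must be "associated with a positive quantitative culture of a respiratory sample", with a threshold for each sampling method.

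On who decides, Assessment criteria says: "Recurrence will be defined with a post hoc analysis by two independent experts with predefined criteria". A third expert settles disagreement, and the Discussion says this assessment is made without knowledge of the arm.

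**The concern.** A limit for leukocytosis should separate raised counts from ordinary ones. The printed limit does not: a count of a few 10⁹/L, including one that would usually be called low, scores as leukocytosis. The sign then carries almost no information, and a rule that asks for two signs is satisfied by any one of the others.

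Two definitions are exposed. At entry, patients with a positive culture but thin clinical evidence of pneumonia could be enrolled. At the endpoint, a positive culture with one further non-specific sign could be scored as recurrence. If such events arise at the same rate in both arms regardless of treatment duration, they shrink a true difference. In a non-inferiority trial that makes it easier to conclude that the short course is acceptable.

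**Working it through.** **1. Units.** One litre is 10⁶ mm³.
- Leukocytosis limit: 10⁹ / 10⁶ = 1,000 per mm³, i.e. 1.0 × 10⁹/L.
- Leukopenia limit: 4 × 10⁸ / 10⁶ = 400 per mm³, i.e. 0.4 × 10⁹/L.

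As printed, a patient fails the sign only with a count from 0.4 to 1.0 × 10⁹/L.

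**2. Slip in the text or damage in extraction?** Both limits look low by the same factor, in two separate sections. The culture thresholds beside them (10³, 10⁴ and 10⁶ CFU/mL) are intact. This points to an error in the article's text.

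**3. How many patients meet the sign.** The document gives no distribution of counts, so this step is an assumption: log-normal counts with median 6 to 15 × 10⁹/L and log-SD 0.35 to 0.7.
- As printed: 99.5% to 100% meet it.
- Both limits ten times higher: about 20% to 88% meet it.

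**4. Effect on the clinical-suspicion rule.** Let each of the other three signs be present independently with probability q (assumed), and the white-cell sign with probability c.
- P(at least 1 of the other 3) = 1 − (1 − q)³
- P(at least 2 of the other 3) = 3q²(1 − q) + q³
- P(rule met) = c × P(at least 1) + (1 − c) × P(at least 2)

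| q | as printed (c ≈ 1) | limits ×10 (c = 0.3 to 0.7) |
|---|---|---|
| 0.2 | 49% | 22% to 37% |
| 0.3 | 66% | 35% to 52% |
| 0.5 | 88% | 61% to 76% |

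If the infiltrate is instead read as mandatory, with two of the remaining three signs needed, two of three becomes one of two. One sign is lost on either reading.

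**5. The plan's own sample size.** Inputs from Statistical analysis: 35.7% in both arms, 10-point margin, α 5%, power 80%. With a one-sided α,

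n = (1.645 + 0.842)² × 2 × 0.357 × 0.643 / 0.10² = 283.8, so 284 per group.

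This matches the stated figure. Allowing for 5% loss, 568 / 0.95 = 597.9, so 598 against the 600 planned. None of this uses the white-cell limits.

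**6. Illustration of dilution.** Take a true excess equal to the margin (35.7% against 45.7%), where non-inferiority should be declared 5% of the time. Suppose a fraction e of patients without a true event is falsely scored as an event in each arm. Each rate p becomes e + (1 − e)p, and the difference becomes (1 − e) × 10 points. With 284 per group,

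P(declare) = Φ[(0.10 − difference) / SE − 1.645].

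| e | long | short | difference | SE | P(declare) |
|---|---|---|---|---|---|
| 0 | 35.7% | 45.7% | 10.0 | 0.0410 | 5.0% |
| 2% | 37.0% | 46.8% | 9.8 | 0.0412 | 5.5% |
| 5% | 38.9% | 48.4% | 9.5 | 0.0414 | 6.4% |
| 10% | 42.1% | 51.1% | 9.0 | 0.0417 | 8.0% |
| 20% | 48.6% | 56.6% | 8.0 | 0.0418 | 12.2% |

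The values of e are chosen, not derived from the misprint. When the true rates are equal, power falls slightly, from 80% to 77.9% at e = 10% and 77.0% at e = 20%.

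**The case against.** The strongest reply is that the article may not show what the trial uses. It condenses a fuller protocol, data go through an e-CRF with consistency checks, and one slip copied between two parallel sentences would explain both occurrences. An intensive care clinician or expert adjudicator would probably notice a limit that almost everyone exceeds. This stands: use of the printed values cannot be confirmed, so any effect on the trial is conditional.

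Three stronger readings are tempting, and the documents do not support them.
- A reader might infer that one sign alone now makes a case. It does not, because a quantitative culture above threshold is still needed. Only the clinical-suspicion part is weakened.
- A reader might infer that purulent secretions with a positive culture, without fever or infiltrate, now count as VAP. That holds if the list is a flat two of four. The wording can also be read as making the infiltrate mandatory, and then this example fails.
- A reader might take 8% to 12% as the error rate caused by the misprint. Those figures rest on assumed false-event fractions of 10% and 20%, which add 6.4 and 12.9 points to the long-duration rate. The planning cohort quoted in the Discussion had 79 recurrences (20.1%) in all. Fractions of 2% or 5% give 5.5% or 6.4%.

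It can also be said that blinded dual adjudication and the exclusion of chronic *P. aeruginosa* colonisation protect the endpoint. They help only in part. Blinding prevents differences between arms in how events are judged, but experts who apply predefined criteria take over whatever limits those criteria contain. The exclusion covers only prior colonisation in COPD or bronchiectasis.

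**Conclusion.** The point holds as an error in the text of two central definitions. The printed limits, 1,000 and 400 cells/mm³, appear low by a factor of ten, and nothing elsewhere in the article corrects them. Taken literally, the white-cell sign is met by nearly every patient, and the clinical-suspicion test loses one sign on either reading of the infiltrate wording. This rests on one assumption from outside the document, that adult counts are several 10⁹/L.

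The consequence for the trial is conditional and its size unknown. If the printed limits are in use, non-specific recurrences unrelated to duration would pull the arms together and favour a finding of non-inferiority. The move from 5% to between 6.4% and 12.2% is only an illustration for assumed false-event fractions of 5% to 20%. Deaths are untouched, and the 284 per group stands.

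**What to change.** 1. Verify the intended limits against the full protocol, the e-CRF and the adjudication documents.
2. Correct Study population and Assessment criteria so that they agree with each other and with those documents. A tenfold shift of both limits would give >10 × 10⁹/L and <4 × 10⁹/L; the investigators must confirm whether that is what was meant. While editing, state whether the infiltrate is mandatory or one of four equal signs.
3. Only if the operational documents carry the printed values: reissue the definition to sites and adjudicators, and re-check randomised patients and adjudicated recurrences whose second qualifying sign was the white-cell count.

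Steps 1 and 2 cost a document check and a one-line correction in two places. Step 3 costs more, but is limited to cases that depended on the white-cell sign. Trial status reports randomisation from June 2016 with inclusion expected until June 2018, so an early check can still protect later enrolment and adjudication.

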### Data analysis

Baseline characteristics of patients will be described per group. Qualitative data will be described with frequencies and percentages; quantitative data will be described with mean and standard error or with median, interquartile interval, and range. Since this is a non-inferiority study, analysis of principal criteria will be performed on a per protocol population. The per protocol population will be defined as randomized patients without major protocol deviations such as non-respect of all selection criteria, clear non-respect of the antibiotic duration allocated (+/– 24 hours), missing data for the primary endpoint, and major protocol deviation(s) identified during a blinded data review before data base freezing. Non-inferiority will be tested by a Dunnett and Gent chi-squared procedure [21]. Secondary analysis in an intent-to-treat (ITT) population will also be performed.

Secondary outcomes will be analyzed under a superiority assumption. Day 30 and day 90 mortality rates and acquisition of MDR pathogens during hospitalization in the ICU will also be compared between groups by a chi-squared test or a Fisher’s exact test, if the use conditions were not verified. Duration of mechanical ventilation, duration of hospitalization in the ICU, duration of exposure to antibiotics, and number of extrapulmonary infections during hospitalization in the ICU will be compared between groups by Student *t* tests or Mann-Whitney/Wilcoxon tests, if needed. Types of extrapulmonary infections will be described.

The association between respiratory colonization with yeast at diagnosis and PA recurrence will be studied by logistic regression adjusted on the randomization group. The association between monotherapy or combination therapy and mortality and PA recurrence will be studied by a logistic regression adjusted on the randomization group. Procalcitonin levels at days 0, 1, 3, and 7 will be described, and their prognosis values on mortality and *P. aeruginosa* recurrence will be studied by logistic regression and sensitivity and specificity analyses. Missing data will be not replaced.

The study will be conducted in accordance with the Helsinki Declaration and French laws and regulations. The study has received its approval from the French ethics committee (Comité de Protection des Personnes Ile de France VI) as well from the French Drug Safety Agency (Agence Nationale de Sécurité du Médicament et des Produits de Santé) (EudraCT 2015-003102-17).

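### Counted over the whole ICU stay, MDR acquisition and extrapulmonary infections include events from before randomisation; this costs precision but favours neither arm

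*Protocol article*

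**What the plan says.** The secondary outcomes under Assessment criteria include "acquisition of MDR pathogens during the hospitalization in the ICU (from swab sample of rectum and anterior nares") and "number and types of extrapulmonary infections during the hospitalization in the ICU". Data analysis keeps the ICU-stay window in the planned tests. MDR acquisition is compared between arms by a chi-squared or Fisher test, and "number of extrapulmonary infections during hospitalization in the ICU" by a t test or a rank test. All secondary outcomes are tested for superiority.

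The timing is set out under Study population. Swabs are taken "at the patient’s admission in the ICU, and then once weekly until the patient’s discharge from the ICU": rectal swabs for ESBL-producing Enterobacteriaceae and nasal swabs for MRSA. Allocation comes later: "The patient will be randomized just after antibiotic susceptibility test results and assigned to the SD arm or the LD arm". The arms then receive different treatment only once the shorter course ends: "All antibiotics would be withdrawn, either at the end of day 8 or day 15".

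**The concern.** By the time of randomisation a patient has been admitted, ventilated, diagnosed with pneumonia, sampled and started on antibiotics. The admission swab is the only reference swab the article names. A patient who is negative at admission and turns positive before randomisation therefore fits the written definition of an acquisition and is credited to whichever arm is drawn. An extrapulmonary infection in the same interval is treated in the same way. The article nowhere starts these counts at randomisation, removes patients already positive by then, or adjusts for them.

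The Discussion presents less antibiotic exposure, and through it less MDR acquisition, as what the short course should achieve. In a superiority test, events that allocation cannot influence make a real reduction harder to detect. A null MDR result could then reflect the counting window and not the strategy.

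A smaller matter of naming goes with this: the outcome is called MDR acquisition, but the swabs look for two organism groups only.

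**Working it through.** **The plan's own figure.** The only design calculation is for the primary composite (Statistical analysis): event rate 35.7% in both arms, margin 10 points, power 80%, α 5%. Taken as one-sided:

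n = 2 × 0.357 × 0.643 × (1.645 + 0.842)² / 0.10² = 283.8, so 284 per arm, as stated. Then 568 / 0.95 = 598, against 600 planned.

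This figure does not depend on the present point. No calculation is given for MDR acquisition.

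**Inputs for MDR acquisition.** From the documents: 600 patients allocated 1:1, so 300 per arm. Assumed, because the documents give no MDR rates: risk of acquisition after randomisation among patients still negative, p_L = 20% (15 days) and p_S = 12% (8 days); share q acquiring between admission and randomisation, the same in both arms, from 5% to 20%. For simplicity all patients are taken as negative at admission.

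**Formulas.**
- Whole-stay risk in each arm: P = q + (1 − q)p.
- Whole-stay risk difference: (1 − q)(p_L − p_S).
- Power, two-sided 5%: Φ{(d − 1.96·SE0)/SE1}, where d is the risk difference, SE0 its pooled and SE1 its unpooled standard error. The whole-stay count uses 300 per arm; the count from randomisation uses 300(1 − q) per arm.

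**Worked case, q = 10%.**
- As written: P_L = 0.10 + 0.90 × 0.20 = 0.280 and P_S = 0.10 + 0.90 × 0.12 = 0.208, so d = 0.072. SE0 = √(0.244 × 0.756 × 2/300) = 0.03507 and SE1 = √((0.2016 + 0.1647)/300) = 0.03494. Power = Φ{(0.072 − 0.0687)/0.03494} = Φ(0.09) = 54%.
- From randomisation, 270 per arm: d = 0.080, SE0 = √(0.16 × 0.84 × 2/270) = 0.03155 and SE1 = √((0.1600 + 0.1056)/270) = 0.03136. Power = Φ{(0.080 − 0.0618)/0.03136} = Φ(0.58) = 72%.

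**Range, 20% against 12%.**

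| q | Whole-stay risks | Difference (points) | Risk ratio | Power as written | Power from randomisation |
|---|---|---|---|---|---|
| 0 | 20.0% / 12.0% | 8.0 | 0.60 | 76% | 76% |
| 5% | 24.0% / 16.4% | 7.6 | 0.68 | 64% | 74% |
| 10% | 28.0% / 20.8% | 7.2 | 0.74 | 54% | 72% |
| 15% | 32.0% / 25.2% | 6.8 | 0.79 | 45% | 69% |
| 20% | 36.0% / 29.6% | 6.4 | 0.82 | 39% | 67% |

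Counted from randomisation, the difference stays at 8.0 points and the risk ratio at 0.60 for every q.

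**Other assumed rates.** With 25% against 15%, power is 69% as written and 83% from randomisation at q = 10%, and 53% and 78% at q = 20%. With 20% against 15%, it is 24% and 33% at q = 10%.

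**Number of extrapulmonary infections.** Infections before randomisation have the same mean in both arms, so the expected difference in means does not change; only the variance rises. As an illustration, take a difference of 0.25 SD, 300 per arm, and an independent pre-randomisation part whose SD is r times the later SD. Power = Φ{0.25/√((1 + r²) × 2/300) − 1.96}, which is 87% at r = 0, 78% at r = 0.5 and 58% at r = 1. The documents give no value for r.

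**The case against.** The strongest reply is that the article gives no start date at all. Reference to the ICU hospitalization may only name the setting and the end of observation. The primary endpoint uses similar words for recurrence, and nobody would count recurrence from admission. Participation is also set at 90 days per patient, which suggests a clock tied to study entry. The full protocol, the analysis plan or the two figures not reproduced here may fix the start.

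That reading is possible, but the article does not state it. A recurrence must follow the index episode by its meaning. An acquisition has no such built-in start, and the swab series it is derived from begins at admission. The window is written into both the outcome definition and the planned test, so it is more than a detail left unmentioned.

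Other parts of the reply stand and limit the point:
- A reader might infer bias, or chance imbalance passing as a treatment effect. Events before randomisation are balanced in expectation, and the test's nominal error rate already covers chance imbalance. The loss is one of precision.
- A reader might extend the dilution to every secondary outcome. Mortality at 30 and 90 days and recurrence are not affected. For "Duration of mechanical ventilation, duration of hospitalization in the ICU, duration of exposure to antibiotics" the article states no start point, which the full protocol may supply; pre-randomisation time would add noise but leave the absolute difference unchanged. "antibiotic-free days during the hospitalization in the ICU" does name the ICU stay, but the same holds there: its day zero needs stating, and dilution of the difference is not shown.
- A reader might take the naming issue to mean that resistance in *Pseudomonas aeruginosa* must be reported. That would be an added endpoint. The article discloses the organisms and swab sites, so only the label is too broad.
- The power figures rest wholly on assumed rates.

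**Conclusion.** The point holds for two outcomes: MDR acquisition and extrapulmonary infections. As written, both can include events that precede allocation. For MDR acquisition the risk difference is multiplied by (1 − q) and the risk ratio moves towards 1. Under the assumed 20% against 12%, power drops to between 64% and 39% as q goes from 5% to 20%, against 74% to 67% when counted from randomisation. At every positive q examined, the restricted count has more power despite its smaller denominator. For the number of extrapulmonary infections the cost is extra variance only.

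The conclusion rests on the literal wording, on equal q in both arms, as randomisation gives in expectation, and on rates the documents do not supply. The primary endpoint, mortality, recurrence and the sample size are untouched. The change is worth making because it is cheap and concerns a benefit the trial expects to show, but the main comparison does not depend on it.

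**What to change.** - Define acquisition separately for ESBL and MRSA as a first positive swab after randomisation, among patients with no earlier positive swab for that organism. A carrier of one then stays at risk for the other.
- Report carriers of each organism at randomisation as a baseline characteristic, by arm.
- Count extrapulmonary infections from randomisation.
- Call the swab outcome ESBL/MRSA acquisition wherever it is defined, tested or interpreted.

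This is a changed derivation from swabs already scheduled, with no new sampling and no change to treatment. Each restriction uses a characteristic fixed before randomisation, so the randomised comparison is preserved. The price is a slightly smaller denominator for each organism. With weekly swabs, some first positives soon after randomisation will still reflect earlier acquisition. Events between randomisation and the end of day 8 also stay in the count, although treatment does not yet differ by arm. The dilution is reduced but not removed.
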